**8.** The autoantibody panel will include antinuclear antibodies (ANA), antineutrophil cytoplasmic antibodies (ANCA), anti-DNA antibody (SS and DS), Rh factor (RhF), antithyroglobulin, anti liver-kidney microsomal (LKM), anti-islet-cell, antibodies to Ro (SSA) and to La (SSB) and antiphospholipid and/or other autoantibody tests.

**9.** Human anti-human antibody may be done at the Investigator’s discretion.

**10.** A total of 2000cGy to be delivered in 5 daily fractions using 6-18 MV photons.

**11.** Immune monitoring will be done using peripheral blood obtained by phlebotomy. PBMC and serum will be isolated and cryopreserved.

**12.** DNA extraction and banking for genomic evaluation.

**13.** Adverse event assessment to be performed continuously throughout the trial. Treatment-related adverse events will be followed until they resolve to baseline or Grade 1 or until the treating physician determines that they are irreversible.

**14.** Patients with measurable disease will be assessed by imaging every 8 weeks until progression (range 6-8 weeks). If a response is seen at week 8, the imaging will be repeated 4 weeks later. The same method of assessment and the same technique should be used for repeated measurements.

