### **7.3.2. Disease Progression Follow-Up**

All patients will be followed for disease progression (if prior SD, PR, or CR) or until the start of a new therapeutic regimen for breast cancer, whichever comes first. This information will be recorded in the CRF. It is understood that not all patients will be available for continued clinic visits; however, every attempt should be made to collect progression date and subsequent therapy (start of therapy).

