## **8.2 Clinical response assessments**

All patients who have qualifying measurable disease outside the radiation field according to RECIST criteria, received investigational treatment, had baseline assessments and at least one on-study tumor assessment will be considered evaluable for response. Data on the response of the irradiated lesion will also be collected.

Tumor assessments will be performed at screening/baseline and then at 6-8 weeks following CP-675,206 dosing. Subjects exhibiting stable disease, partial response or complete response at the 8 week timepoint will undergo confirmatory re-evaluation 4-6 weeks following the first documented response. Patients may also be evaluated at 12 weeks following treatment. The same method of assessment and the same techniques used at screening must be performed.

Patients who were treated and removed from the trial prior to on-study tumor assessment for reasons such as patient request, lack of compliance, or as early toxicity (patients who went off study due to serious adverse events related to the trial drug therapy prior to reassessment of tumor lesions) will not be considered evaluable for the secondary objective of efficacy of the trial. Patients who discontinue treatment with stable disease or an unconfirmed response, who subsequently have a response confirmed prior to starting new treatment, will be classified as responders. If no confirmation is obtained, they will be considered as non-responders.

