### **8.2.2. “Target” and “Non-Target” Lesions**

Baseline tumor measurements must be performed not more than 4 weeks (28 days) prior to the initiation of treatment with CP-675,206. Patients must have at least one measurable lesion outside of the radiation field at baseline to be included in the analysis of this endpoint. If the measurable disease is restricted to a solitary lesion, its neoplastic nature could be confirmed by cytology/histology if necessary.

Baseline documentation of tumor sites may include imaging assessment of disease in the chest, abdomen and pelvis. A baseline imaging study of the brain is required.

Target Lesions

• Up to 10 total lesions, a maximum of 5 lesions per organ, that are representative of all involved organs may be selected and recorded as target lesions at baseline. Target lesions should be selected on the basis of their size (lesions with the longest diameter) and their suitability for accurate repetitive measurements (either by imaging techniques or clinically). A non-measurable lesion cannot be selected as a target. A sum of the longest diameter (LD) for *all target lesions* will be calculated and reported as the baseline sum LD. The baseline sum LD will be used as reference to further characterize the objective tumor response of the disease.

Non-Target Lesions

• All other lesions (or sites of disease) should be identified as non-target lesions and recorded as non-target lesions at baseline. Measurement of non-target lesions at baseline is not required and should be recorded as “present.” Each non-target lesion should be documented as either present, absent or new in each subsequent evaluation.

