### **8.2.5. Frequency of Tumor Measurements**

Tumor assessments will be performed every 6 to 8 weeks. CR and PR must be confirmed by repeat assessments performed 4-6 weeks after the criteria for response are first met to qualify as such response. Additional tumor measurements may be completed as needed.

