### **8.2.6. Evaluation of Overall Response**

The best overall response is the best response recorded since the start of treatment until disease progression or recurrence (taking as reference for PD the smallest measurement since treatment started). For CR and PR the best response assignment will depend on the achievement of both the initial establishment and confirmation of CR or PR.

To be assigned a status of Partial Response (PR) or Complete Response (CR), changes in tumor measurements must be confirmed by repeat assessments that should be performed no less than 4 weeks after the criteria for response are first met, per RECIST.If a patient does not achieve a PR or CR but maintains Stable Disease (SD) for at least 10 weeks or more, then the best overall response for the patient will be SD.

| Overall Response | | | |
| --- | --- | --- | --- |
| Target Lesions | Nontarget lesions | New Lesions | Overall response |
| CR a | CR | No | CR |
| CR | Non-CR/Non-PD | No | PR |
| PR b | Non-PD | No | PR |
| SD c | Non-PD | No | SD |
| PD d | Any | Yes or No | PD |
| Any | PD | Yes or No | PD |
| Any | Any | Yes | PD |
| a, Complete Response  b, Partial Response  c, Stable Disease  d, Progressive Disease | | | |

##

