## **10.5. Analysis of Secondary Endpoints**

### **10.5.1. Efficacy Analyses**

#### 10.5.1.1. Best Overall Response

For patients with measurable disease, best overall response will be defined according to the Response Evaluation Criteria in Solid Tumor (RECIST) guidelines. For patients without measurable disease, best overall response can be a CR (no evidence of disease), PR (eg unequivocal progression in non-measurable lesions or new lesion), or SD in all other cases. Listing of patients with their measurability status at baseline and best overall response on study will be provided.

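### Section 10.5.1.1 gives patients without measurable disease a best overall response that Sections 8.2 and 8.2.2 do not allow, and makes stable disease the residual category with no not-evaluable option

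*Protocol*

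**What the plan says.** **Who counts for response.** Section 8.2 requires measurable disease outside the radiation field and adds that such patients who "had baseline assessments and at least one on-study tumor assessment will be considered evaluable for response". Section 8.2.2 repeats the first condition: "Patients must have at least one measurable lesion outside of the radiation field at baseline to be included in the analysis of this endpoint". Section 8.2 also makes patients who leave the trial before an on-study tumor assessment not evaluable for efficacy.

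**What stable disease needs.** Under Section 8.2.6, SD is the best overall response of a patient who has no CR or PR but "maintains Stable Disease (SD) for at least 10 weeks or more".

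**What the analysis section does.** Section 10.5.1.1 applies RECIST to patients with measurable disease. It then gives a separate rule for the others: CR, a category labelled PR, "or SD in all other cases". It promises a listing of patients by measurability at baseline and best overall response.

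**When tumors are assessed.** Section 8.2: "Tumor assessments will be performed at screening/baseline and then at 6-8 weeks following CP-675,206 dosing". Section 8.2.5: "Tumor assessments will be performed every 6 to 8 weeks". Neither sentence is limited by measurability. Note 14 to Table 2 (printed in Sections 7.2 and 13) reads: "Patients with measurable disease will be assessed by imaging every 8 weeks until progression (range 6-8 weeks".

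**Progression.** Section 7.3.2 states "All patients will be followed for disease progression". Section 10.5.1.3 defines PFS from enrollment with no measurable-disease condition, and Section 10.1 defines only an as-treated population.

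**The concern.** Section 10.5.1.1 is a stated rule, so this is not a detail left for a later analysis plan. It conflicts with Section 8 on two counts. It classifies patients whom Section 8 excludes from the response analysis. It also makes SD the category for everyone not otherwise described, so that a missing assessment and an observed stable course receive the same label.

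The eligibility criteria in Section 5.1 do not require measurable disease, so such patients can be enrolled. Section 2.1.1 names bone as the most frequent site of palliative radiation and Section 8.2.1 classes bone lesions as non-measurable. That makes the group plausible without giving its size.

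Three things are at stake: the best-response listing, PFS, and the exploratory correlation of immune data with clinical responses in Section 10.5.2.1. Efficacy is a secondary objective. The DLT and MTD rules do not use any of this.

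**Working it through.** No stated figure is in dispute, so the check is a comparison of rules plus one date calculation.

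**1. The same course under the two sets of rules**

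| Course on study | Sections 8.2 and 8.2.6 | Section 10.5.1.1, no measurable disease, read literally |
| --- | --- | --- |
| Removed before any on-study tumor assessment | Not evaluable | SD |
| Stays 12 weeks, no on-study tumor assessment | Not evaluable (needs at least one assessment) | SD |
| One assessment at week 8 without progression, none later | 8 weeks is below 10 weeks, so SD is not met | SD |
| No CR and no progression, documented for 10 weeks or more | SD | SD |

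The rules agree only in the last row. In the first three, 10.5.1.1 produces SD where Section 8 does not. (The middle column ignores the further bar in 8.2 and 8.2.2, under which a patient without measurable disease outside the field is not in the response analysis at all.)

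**2. Whether Section 8 closes the gap by itself**

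The not-evaluable rule in 8.2 covers patients removed from the trial before an on-study assessment. It contradicts the residual rule for row 1. It does not reach row 2, where the patient was never removed. The 10-week condition in 8.2.6 is worded for any patient, but 10.5.1.1 sets up a separate rule for this group without referring to it. The two sections therefore give different answers, and nothing states which governs.

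**3. Assessment schedule**

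Table 2 has one post-baseline imaging cell, at D57. Its note 14 speaks of patients with measurable disease and says nothing of the rest. Sections 8.2 and 8.2.5 schedule assessments for all. A site following 8.2 would assess a bone-only patient at 6 to 8 weeks; a site following only note 14 has no instruction to image that patient again.

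**4. Consequence for PFS if there is no post-baseline assessment**

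Section 10.5.1.3 censors on the day after the last tumor assessment showing no progression, and the clock starts at enrollment. Section 8.2.1 allows the baseline evaluation up to 28 days before enrollment. If that evaluation is the only one, and is done s days before enrollment:

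- censoring time = 1 − s days
- s = 0 gives +1 day; s = 28 gives 1 − 28 = −27 days

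The patient then adds essentially no follow-up, and the computed time can be negative. This needs two conditions: no later tumor assessment of any kind, and no death or documented progression.

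**5. Number affected**

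Section 10.2 expects 6 to 32 patients. The protocol gives no share without measurable disease outside the field, and none without an on-study assessment. The count cannot be computed.

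**The case against.** A reader might infer that patients without measurable disease get no scan and are therefore all recorded as SD by default. The documents do not support that, for four reasons.

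- Note 14 is silent about these patients; it does not exempt them. Sections 8.2 and 8.2.5 schedule tumor assessments without restriction.
- A patient who leaves early is already not evaluable under 8.2, and the 10-week condition in 8.2.6 is not confined to measurable disease.
- SD is not the only reachable outcome. Section 8.2.2 has non-target lesions recorded as present, absent or new at each evaluation, Section 8.2.3 accepts clinical examination, and physical examinations run from D8 to D85. Progression can be documented without a scan. Because PFS refers to the last tumor assessment and not the last scan, censoring at baseline is not automatic.
- The protocol specifies no SD count, disease-control rate or response rate. The listing already shows measurability status, and no efficacy decision rule feeds phase II.

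All four points stand, and they limit the claim. They do not remove it. That Section 8 contains the right conditions is what makes 10.5.1.1 contradictory: its residual rule covers all other cases and has no not-evaluable category. A patient who stays on trial unassessed is not reached by the rule for removed patients. Note 14 and Sections 8.2 and 8.2.5 still need to agree on who is assessed.

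**Conclusion.** Section 10.5.1.1 is wrong as written, on a limited scale. It assigns a best overall response to patients whom 8.2 and 8.2.2 exclude, and its SD category omits the on-study assessment of 8.2 and the 10 weeks of 8.2.6. Taken literally, it turns absent or short follow-up into SD.

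The schedule conflict is real, but its effect on PFS is conditional. Censoring at or near time zero arises only if a site follows note 14 alone and no clinical tumor assessment fills the gap. It should not be read as the expected course for every patient with non-measurable disease, nor should bone as the most frequent radiation site be read as an estimate of how many there are: such patients may have measurable lesions elsewhere.

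The number affected is unknown. The effect is confined to the secondary efficacy listing, PFS and the exploratory correlation with clinical responses. The primary safety and MTD analysis does not depend on it. The correction is worth making because it changes how individual patients are classified and costs almost nothing.

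**What to change.** 1. In Section 10.5.1.1, for patients without measurable disease, replace the residual SD rule with: *non-CR/non-PD if at least one on-study tumor assessment shows neither CR nor progression and the duration in Section 8.2.6 is met; otherwise not evaluable.* Say that these patients are listed but kept out of the response analysis, as 8.2.2 states.
2. Make this edit together with the correction of a separate error in the same sentence, where unequivocal progression or a new lesion is labelled PR and PD is missing. Correcting that label alone would leave the residual SD rule in place.
3. Reconcile note 14, in both printings of Table 2, with Sections 8.2 and 8.2.5, so that one rule says who has on-study tumor assessments. Otherwise, state in Section 10.5.1.3 that PFS is limited to patients with on-study tumor assessments.

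**Cost.** Protocol wording only. Fewer patients may be listed as SD. Aligning note 14 with 8.2 and 8.2.5 adds no assessment that those sections do not already state; limiting PFS instead reduces the number of patients in that analysis. The duration condition is workable: 8.2 already calls for re-evaluation of stable disease 4 to 6 weeks after the week-8 assessment, that is at 8 + 4 = 12 to 8 + 6 = 14 weeks, beyond the 10 weeks required.

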#### 10.5.1.2. Duration of Tumor Response

Duration of Objective Response (CR or PR) will be measured from the date that a CR or PR is first documented (whichever occurs first) to date of progression or death due to progressive disease, whichever occurs first.

Duration of Complete Response will be measured from the date that a CR is first documented to date of progression or death due to progressive disease, whichever occurs first.

Patients last known to be progression-free are censored at the date they were last known to be progression-free, with the following exceptions.

**1.** Patients who go off treatment prior to progression will continue to be followed for progression until a new treatment is initiated. The date of new treatment will be used as the progression date unless the patient has clearly not progressed by the time of new treatment, as judged by the Investigator. If the patient has clearly not progressed, censorship will be at the date of the new treatment.

**2.** Patients who die of causes clearly not related to disease before progression, as judged by the Investigator, will be censored at date last known to be progression-free. Otherwise date of death will be used as the progression date.

#### 10.5.1.3. Progression-free Survival

Progression-free survival (PFS) is defined as the time from the date of enrollment to the date of first documentation of disease progression, or to the death from any cause. PFS data will be censored on the day following the date of last tumor assessment documenting absence of progressive disease for patients who do not have objective tumor progression and are still on trial at the time of an analysis, are given antitumor treatment other than the trial treatment, or removed from trial follow-up prior to documentation of objective tumor progression. Kaplan-Meier method will be used to obtain median PFS.

### **10.5.2. Analysis of Other Endpoints**

#### 10.5.2.1. Immune monitoring

Summary statistics (mean, median, standard deviation, quartiles, minimum and maximum, etc.) will be provided for evaluations of immunological responses as appropriate. These data will also be used to explore any correlation with the dose of CP-675,206 and clinical responses.

### **10.5.3. Interim Analysis**

An interim analysis of safety is planned after the second dose level is complete.

# 11. DATA HANDLING AND RECORD KEEPING

All source data and documents generated in their trial will be made available to trial-related monitoring, audits, Research Ethics Boards (REB) review and regulatory inspections as required.

## **Retention of Patient Records and Study Files**

The Therapeutic Products Directorate of Health Canada states in its *Good Clinical Practice: Consolidated Guidelines (ICH Guidance Document E6)* (1997) that the investigator and sponsor shall retain study records relating to the study until at least 2 years after the last approval of a marketing application and until there are no pending or contemplated marketing applications, or at least 2 years have elapsed since the formal discontinuation of clinical development of the investigational product. In the event of a trial discontinuation, sponsor records should also be kept for a minimum of 2 years. Records contained in the Clinical Trial Application should be maintained on file for at least 25 years. We will comply with these regulations.

#

# 12. ETHICS

## **12.1. Research Ethics Board Approval for Protocols**

*Initial Approval.* The protocol and consent forms will receive full ethics board approval by the University Health Network REB prior to commencement of the clinical trial.

*Continuing Approval.* Annual re-approval will be sought for as long as the trial is open to patient accrual.

*Amendments.*  An amendment to a protocol which constitutes a significant change will be submitted to review/approval by local REBs and, if applicable, by the Biological and Genetic Therapies Directorate of Health Canada, as required.

## **Informed Consent**

*Informed consent document.* The REB of an institution must approve the consent form that will be used at that centre prior to its local activation; changes to the consent form in the course of the study will also require REB notification/approval.

The following elements must appear in the consent form: a description of the purpose of the study (indicating, if appropriate, that the therapy is investigational); potential side effects, potential benefits; study design; voluntary participation; and confidentiality. It is essential that the consent form contain a clear statement which gives permission for 1) information to be sent to and 2) source medical records to be reviewed by government agencies as necessary. The consent forms attached to this document meet these requirements.

*Consent process/patient eligibility*. Patients who cannot give informed consent (i.e. mentally incompetent patients, or those physically incapacitated such as comatose patients) are not to be recruited into the study. Patients competent but physically unable to sign the consent form may have the document signed by their nearest relative or legal guardian. Each patient will be provided with a full explanation of the study before consent is requested.

# 13. TABLES

## **Table 1. Pre-trial assessments**

| **Assessment/Test** | **Within 72 Hours** | **Within 5 days** | **Within 14 Days** | **Within 28 Days** |
| --- | --- | --- | --- | --- |
| Obtain Informed Consent |  |  | X |  |
| Medical History1 |  |  | X |  |
| Baseline Signs & Symptoms2 |  |  | X |  |
| Enrollment |  | X |  |  |
| Height |  |  | X |  |
| Weight |  |  | X |  |
| Physical Exam, including vital signs and clinical signs of autoimmunity3 |  |  | X |  |
| Review of Concomitant Medications4 |  |  | X |  |
| ECOG status |  |  | X |  |
| ECG |  |  | X |  |
| Pregnancy Test (serum or urine) for women of childbearing potential (WOCBP)5 | X |  |  |  |
| Hematology6 |  |  | X |  |
| Serum Chemistry7 |  |  | X |  |
| Total IgG |  |  | X |  |
| Microscopic Urinalysis8 |  |  | X |  |
| Thyroid Function9 |  |  | X |  |
| HIV, Hepatitis screening10 |  |  | X |  |
| HLA Typing |  |  | X |  |
| Adverse Events |  |  | X |  |
| Tumor Imaging (CT, MRI)11 |  |  |  | X |

**1.** Includes review of systems, oncologic history and general medical history of all disease processes (active or resolved), and concomitant illnesses. Disease characteristics include diagnosis, date of diagnosis, cytology or histology, stage at time of trial entry, and breast cancer treatment history.

**2.** The Investigator should describe any signs and symptoms at presentation reported by patients during the 14 days prior to the initial dose of CP-675,206. Patients should be questioned about visual symptoms. Any patient who is experiencing symptoms suggestive of uveitis or melanoma-associated retinopathy (eg eye pain or redness, sensitivity to light or glare, blurred vision, floaters, night blindness, or visual field defects) should be evaluated by an ophthalmologist to rule out these conditions.

**3.** The physical exam should be performed by an Investigator at baseline, and a physician or designee may perform subsequent assessments, as appropriate. Vital signs include temperature, blood pressure, heart rate while sitting

**5.** Must be negative within 72 hours prior to the initial dose of CP-675,206.

**4.** All concomitant medications taken within 14 days need to be documented and recorded (including start and stop dates, as appropriate) on the patient CRF.

**6.** Hemoglobin, WBC with 5-part differential (percent and absolute values), platelet count.

**7.** Calcium, chloride, total protein, potassium, random glucose, sodium, blood urea nitrogen/BUN, creatinine, AST/SGOT, ALT/SGPT, alkaline phosphatase/ALP, lactic acid dehydrogenase/LDH, amylase, lipase, albumin, total bilirubin

**8.** Collect urine for Urinalysis [must include: 1) microscopic analysis of urinary sediment and 2) analysis for protein, glucose, and blood (other, as indicated)].

**9.** Thyroid stimulating hormone (TSH), T3, T4.

**10.** Refer to Exclusion Criteria.

**11.** Documentation of Baseline target and non target lesions by imaging techniques or by measurement of clinical lesion(s) must be performed within 28 days prior to dosing. The method of tumor assessment (CT, MRI) and tumor sites are to be consistent from baseline to the end of the study.

